#### Subjective health-related quality of life (HRQOL)

*World health organization quality of life instruments–BREF*. The World Health Organization Quality of Life Instruments–BREF (WHOQOL-BREF [74]) questionnaire, validated for the Portuguese population [75], assesses the subjective quality of life. WHOQOL-BREF includes 26 questions (with structured responses on a 5-point Likert scale) of which two are more general, related to the general perception of the quality of life and the general perception of health, and the remaining 24 comprise physical, social relations, environment, and psychological domains [75, 76]. To calculate the final score, it is necessary to invert items 3, 4 and 26. The final score should be converted into a scale from 0 to 100, with a higher score corresponding to a better perception of quality of life [75, 76].

*Satisfaction with life scale*. The Satisfaction with Life Scale (SWLS [77]), validated for the Portuguese adult population [78], assesses a person’s global judgment of life satisfaction. SWLS comprises 5-item formulated in the positive sense, with structured responses on a 7-point Likert scale (range from level 1 to 7, strongly disagree to strongly agree, respectively) [77, 78]. Final results range between 5 (low satisfaction) to 35 (high satisfaction) [77].

*Perceived stress scale*. The Perceived Stress Scale (PSS [79]), validated for the Portuguese adult population [80], measures the person’s life situations, assessed as stressful. The 14-items on the scale are created to assess the degree to which subjects believe that their life is unpredictable, out of control and overloaded, during the previous month [80]. PSS also includes several direct queries about current levels of experienced stress [80]. Of the 14-items, seven are considered negative and the other seven as positive, all rated on a 5-point Likert scale [80]. To calculate the final score, it is necessary to take into attention that items 4–7, 9, 10 and 13 refer to positive situations, being necessary to invert the quotation [79, 80]. Results range between 0 to 56 points, with a higher score representing higher levels of stress [80].

*36-item short form survey*. The 36-Item Short Form Survey (SF-36 [81]), validated for the Portuguese adult population [82, 83], is a generic instrument to evaluate HRQoL. This instrument comprises 36 questions which cover 8 subdomains of health, namely: physical functioning (PF), role-physical (RP), role-emotional (RE), bodily pain (BP), general health (GH), vitality (VT), social functioning (SF), and mental health (MH) [81–83]. These 8 subdomains can be grouped into two component scores, namely: a physical component summary and a mental component summary. Dimension scores are presented on a positively oriented scale from 0 (poor health status) to 100 (good health status). Higher scores on both subscales represent better health and functioning [81].

#### Secondary outcomes

*Anthropometry and body composition*. Body mass will be assessed using a portable scale (SECA 761, Germany) with accuracy to the nearest 0.1 kg while wearing minimal clothes. Stature will be determined using a portable stadiometer (Seca Bodymeter 208, Germany), with accuracy to the nearest millimeter, according to the standardized procedures [84]. The body mass index (BMI) will be calculated according to the usual formula: BMI = (weight/height ^2^). Waist circumference (WC) will be assessed twice using a flexible tape measure (Hoechstmass-Rollfix, Germany) made of fiberglass, with an accuracy of 0.1 cm and according to the standardized procedures of the National Institute of Health [85]. If the two WC measurements differ by ≥ 0.5 cm, a third measurement is taken, and the mean circumference will be calculated from the two nearest measures. Values of skeletal muscle mass (kg), fat mass (kg), bone mineral mass (%), and body fat (%) will be determined using the tetrapolar bioimpedance (Inbody 270, USA). The participants age, sex, and stature will be entered into the bioimpedance scale. The impedance measurements will be performed according to the literature [86], removing the watch or any other metallic object from the participants. These measures will be conducted between 09:00 and 11:00 a.m. by invited specialists and co-investigators of the research team.

*Physical fitness*. ***Cardiorespiratory fitness (CRF)***. The “Chester Step Test” will be conducted using audio (with stepping beat rhythms) and a step (height, 15, 20, 25, or 30 cm, depending on the age and physical ability of the subject [87, 88]). The participant is required to step to the beat rhythm at 15 steps/min for 2 minutes following which HR and RPE are recorded (Level 1) [87]. Every 2 minutes the stepping rate increase slightly by 5 steps/min, and the HR and RPE are again recorded [87]. The test continues in this progressive mode until the participant achieves 80% of their HR_max_ or reports a moderately vigorous level of exertion (RPE = 14) [88]. The maximum test duration is 10 min, which corresponds to the last level of the test (i.e., Level 5). Maximal oxygen consumption (VO_2_max) will be calculated using the CST software (Cartwright fitness, UK) [88].

***Muscle strength***. “Hand Grip Test”–Handgrip strength will be assessed using a hand dynamometer (Jamar, Lafayette Instrument Company, USA) to the nearest 0.1 kg. The participant starts by adjusting the grip bar, so the second joint of the fingers fits under the handle [55]. Measurements will be taken with the participant standing with arms parallel to the body. The participant squeezes the handgrip dynamometer as hard as possible, without holding the breath [55]. The handgrip test will be repeated twice in each hand and the final score will be the highest of the two readings (to the nearest kilogram) for each hand added together [55].

***Arms flexibility***. “Back Scratch test”–This test was developed by Rikli and Jones [89] to measure flexibility in the shoulder joint and shoulder arch on the right and on the left side. The participant will place a hand over the shoulder of that same arm in the direction of the floor, and the other hand up the middle of the back in the direction of the head [89]. Then, the participant tries to touch or overlap the fingers of both hands. The distance in centimeters (+ or -) between the extended middle fingertips of each hand will be registered [89]. Two attempts will be taken on each side (right and left arm over), and the final score will be the mean of the two measures (to the nearest half cm) [89].

***Legs flexibility***. “Modified sit-and-reach test”–This test was developed by Hoeger and Hopkins [90] to evaluate hamstring and low-back flexibility. This test requires a sit-and-reach box (height, 30.5 cm) and a ruler (range of 0 to 70 cm). The participant sits on the floor with the head, back and hips in contact with the wall and the feet with the sit-and-reach box [90, 91]. Participants will be asked to overlap hands (with middle fingers on the same level) and to execute a scapular abduction to reach out level with the measurement scale. Then, the ruler is moved along the box until the zero point of the ruler is even with the tip of the fingers—finger to box distance (FBD) [90, 91]. FBD represents a relative zero point for each subject based on proportional differences in limb lengths [90]. With FBD established, the participant slowly leans as far forward as possible, allowing the head and shoulders to stop having contact with the wall and the fingers to slide over the ruler [90]. The distance between the “0 cm” point and the end point will be recorded [90]. Two measurements will be performed, and the final score will be the mean of the two measures (nearest half cm). All measures of physical fitness will be conducted between 09:00 and 11:00 a.m. by invited specialists and co-investigators of the research team.

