## Abstract

**Background:**

Both physical inactivity and sedentary behavior are considered modifiable risk factors for chronic diseases and all-cause mortality. Adult office-workers spend most of their working day in sedentary behaviors, so they are particularly at high risk of developed chronic diseases (e.g., cardiovascular diseases, metabolic disorders like diabetes mellitus, …). It seems important to promote behavioral changes that could prevent or delay metabolic disease development. Evidence supports the use of exercise programs, however, to date there are several knowledge gaps and inconsistencies in the literature regarding the effects of Combined Training (i.e., aerobic plus resistance training) in sedentary healthy adults. This paper outlines an RCT designed to evaluate the effects of a 16-week combined training program on biochemical and immune markers of metabolic disease, lung function, salivary stress hormones and subjective quality of life (primary outcomes), as well as on body composition and physical fitness (secondary outcomes) in sedentary middle-aged office-workers. Furthermore, we aimed to assess the associations between the changes promoted by the exercise program and the different variables studied.

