*Brachial blood pressure*. The right and left brachial systolic blood pressure (SBP) and diastolic blood pressure (DBP) will be measure using an automated oscillometric cuff (OMRON, HEM 907, Japan). The participant will be comfortably seated, with the legs uncrossed and the back and arm supported, for 3–5 minutes without speaking and/or moving before recording the first measure [69, 70]. Two readings will be taken at intervals of at least 1–2 minutes and the average of those readings will be recorded as the participant’s BP. However, if the values deviate by ≥ 5 mmHg, a third measurement will be performed, and the average of these multiple readings will be used [69, 70]. The participants must avoid caffeine, physical exercise, and smoking for at least 30 minutes prior to measurement [69]. The brachial BP will be assessed in the morning (between 09:00h – 12:00h) and will be performed by a doctor.

*Lung function*. Spirometry will be conducted using the Spiropalm 6MWT (Cosmed, Italy) Spirometer. Participants will perform a maximal inspiratory and expiratory maneuver to achieve the Forced Vital Capacity (FVC), Forced Expiratory Volume in 1 second (FEV_1_), and Peak Expiratory Flow (PEF). Participants’ data will be classified to indicate repeatability. In this sense, the participants will have to complete at least three acceptable FVC maneuvers to be included in the analysis (i.e., the difference between the best two FEV_1_ and FVC values must be within 150 mL) [71, 72]. The best FEV_1_ and best FVC measures of the participants will be recorded and used for data analysis, according to procedures adopted in other studies [20, 21]. Predicted FEV_1_ (FEV_1_% pred), predicted FVC (FVC% pred), and predicted PFE (PFE% pred) will be calculated based on age, stature, ethnicity, and sex using the formulas developed by the Global Lung Function Initiative [73]. The lung function assessment will occur in the morning (between 09:00h – 12:00h) and will be performed by a doctor.

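### After a triggered third waist reading, the median of the three would nearly always be more precise than the planned mean of the two nearest; the gain is small and free

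*Protocol article*

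**What the plan says.** Under Secondary outcomes (Anthropometry and body composition) the protocol article states: "Waist circumference (WC) will be assessed twice using a flexible tape measure", "with an accuracy of 0.1 cm". The trigger is "If the two WC measurements differ by ≥ 0.5 cm"; then "a third measurement is taken, and the mean circumference will be calculated from the two nearest measures". The rule is executable for nearly all triplets and makes no distinction between arms.

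Waist belongs to the body-composition set, which the abstract ranks as secondary: "as well as on body composition and physical fitness (secondary outcomes". The schedule (Table 3) places body composition at baseline, mid-testing and post-testing.

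For blood pressure, under Primary outcomes, the handling of a third reading is different: "a third measurement will be performed, and the average of these multiple readings will be used".

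The article gives no SD or distribution for waist reading error and makes no claim about the precision of the rule.

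**The concern.** Dropping the reading that lies furthest from the others looks like removal of an error. If reading errors are ordinary and roughly normal, the dropped reading is often a good one, and the two that are kept may agree by chance on the same side of the true value. The extra reading may then buy less precision than it could, or even cost some.

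At stake is measurement noise in waist circumference, the body-composition measure closest to abdominal obesity, which the Introduction names as a metabolic risk marker. Noise in change scores widens the between-group comparison and weakens the planned correlations between changes.

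**Working it through.** **Inputs from the protocol.** Two routine readings; 0.1 cm resolution; third reading if |x1 − x2| ≥ 0.5 cm; score is then the mean of the two nearest. There is no stated precision figure to reproduce.

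**Assumed inputs.** Independent reading errors with SD s of 0.3 to 1.0 cm, under several distributions; true-change SD of 2 to 3 cm.

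**Step 1: closed form, normal error, three readings always taken.** The midpoint of the closest pair has variance

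s² × [1/3 + (1/3)(1/2 + 3√3/(4π))] = s² × [0.333 + (1/3)(0.500 + 0.413)] = 0.638 s².

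The mean of two has 0.500 s² and the mean of three has 0.333 s². So with normal error the closest pair is worse than any two readings taken blindly (0.638/0.500 = 1.28).

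**Step 2: the rule as written.** Two million triplets were simulated per setting, recorded to 0.1 cm, with the third reading used only when triggered and ties for the nearest pair broken at random. Error variance (cm²) among triggered assessments; the last column is taken before rounding:

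| Assumed reading error | Triggered | First two | Two nearest | Median of 3 | Mean of 3 | Median vs two nearest |
|---|---|---|---|---|---|---|
| Normal, SD 0.3 | 29% | 0.045 | 0.081 | 0.051 | 0.030 | −38% |
| Normal, SD 0.5 | 52% | 0.125 | 0.189 | 0.120 | 0.083 | −36% |
| Normal, SD 1.0 | 75% | 0.501 | 0.685 | 0.452 | 0.334 | −34% |
| Laplace, SD 0.5 | 46% | 0.187 | 0.154 | 0.104 | 0.111 | −33% |
| SD 0.5, 2% of readings at 5×SD | 54% | 0.235 | 0.196 | 0.132 | 0.146 | −33% |
| SD 0.5, 5% of readings at 5×SD | 56% | 0.390 | 0.217 | 0.155 | 0.235 | −29% |
| SD 0.5, 10% of readings at 5×SD | 59% | 0.624 | 0.276 | 0.206 | 0.372 | −25% |
| SD 0.3, 1% of readings off by 5 cm | 30% | 0.454 | 0.091 | 0.063 | 0.239 | −31% |
| SD 0.5, 5% of readings off by 5 cm | 57% | 1.197 | 0.352 | 0.270 | 0.698 | −23% |

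Three things follow.

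- Two nearest against the first two: worse in the three normal rows, better in all the others.
- Two nearest against the mean of three: worse in five rows, better in four (the 5% and 10% rows at 5×SD, and both rows with 5 cm errors).
- Two nearest against the median: worse in every row. Across about 90 settings there was one exception, a reading SD of 0.1 cm with 1% of readings shifted by 1 cm (0.0135 against 0.0151 cm²), where only about 2% of assessments trigger.

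**Step 3: effect on the change score, normal error.** Untriggered assessments keep the mean of two, with variance 0.5 s². Per-visit error variance:

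- s = 0.5, stated rule: 0.525 × 0.189 + 0.475 × 0.125 = 0.159. Median: 0.525 × 0.1205 + 0.475 × 0.125 = 0.123.
- s = 1.0, stated rule: 0.75 × 0.685 + 0.25 × 0.5 = 0.639. Median: 0.75 × 0.452 + 0.25 × 0.5 = 0.464.

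Variance of change = true-change variance + 2 × per-visit error variance. Stated rule over median:

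- s = 0.5: true SD 2 gives 4.318/4.246 = 1.017; true SD 3 gives 9.318/9.246 = 1.008.
- s = 1.0: true SD 2 gives 5.278/4.928 = 1.071; true SD 3 gives 10.278/9.928 = 1.035.

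At the largest of these, a confidence interval is √1.071 = 1.035 times as wide, and a correlation with the waist change shrinks by the factor 1/√1.071 = 0.966. At 1.017 the figures are 1.008 and 0.992.

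**Step 4: ties.** With 0.1 cm recording and normal error, about 4 to 6% of triggered triplets are equally spaced, for example 90.0, 90.3, 90.6. No pair is then nearest and the rule gives no answer; the median does.

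**The case against.** The strongest defence is that the rule is aimed at a misplaced or misread tape, so judging it under normal error assumes away what it guards against. This stands as far as it goes. A reader might infer from the normal-error results that the third reading makes waist worse than ignoring it. The documents do not support that as a general statement: they give neither the size nor the shape of the reading error, and with 5% of readings at five times an SD of 0.5 cm the stated rule roughly halves the error variance relative to the first two readings (0.217 against 0.390 cm²).

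The defence does not rescue the rule against the median, which also resists a single bad reading and did better in every gross-error setting tabulated.

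A reader might also infer that the waist and blood-pressure rules contradict each other. They do not. They cover different measures with different instruments, and the protocol uses further rules elsewhere, such as the highest reading for grip and the mean for flexibility. Nor does the blood-pressure rule show that all three waist readings should be averaged, since that average can lose to the stated rule under gross errors.

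Finally, it can be said that no trial conclusion would turn on this. That is fair, and it limits the point to a minor one.

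**Conclusion.** The point holds as a minor refinement. Whether the two-nearest mean beats the first two readings alone depends on an error distribution that the protocol does not give: it loses with roughly normal error and can win with heavy tails or gross errors. What holds across almost all assumed models is that the median of three is more precise, by about 20 to 40% of the error variance in triggered assessments. One narrow exception was found.

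On the change score the difference is roughly 1 to 2% of variance at a reading SD of 0.5 cm and 4 to 7% at 1.0 cm, given a true-change SD of 2 to 3 cm. All of these SDs are assumptions. No different rule is stated for either arm, so the effect is added noise and not bias, and it touches one secondary measure. The plan contains no contradiction on this point.

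**What to change.** In the waist procedure, keep the two readings and the 0.5 cm trigger, and change the scoring after a third reading from the mean of the two nearest to the median of the three measures. Do not switch to the mean of all three: it is the most precise choice under normal error but can do worse than the present rule when a reading is grossly wrong.

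The cost is one phrase in the measurement procedure, with no extra readings, staff or participants. It also settles the equally spaced triplets. The new rule should apply to all three assessment times; if individual readings are kept, earlier scores can be recomputed.

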#### Supportive measures

*Levels and patterns of physical activity and sedentary behaviour*. Sedentary time and PA levels (light-, moderate-, and vigorous intensity) will be assessed using a triaxial accelerometer (Actigraph GT3X, Actigraph Corporation, Florida, USA). Accelerometers will be initialized to capture data at 100 Hertz using ActiLife software V6 13.3 (ActiGraph, Florida, US), and the data will be recorded in 60-s epochs [92]. Participants will be instructed to wear the device on their waist near the right iliac crest during all waking hours for 7 consecutive days (i.e., 5 weekdays and 2 weekend days), except when sleeping, bathing, or swimming [92, 93]. Non-wear time will be defined as ≥ 60 minutes of consecutive zero accelerometer counts (allowing up to 2 minutes with limited movement) [92, 94]. All participants with at least 4 days with 600 min (10 h) of wear time per day will be included in the analysis [92, 94, 95]. To classify accelerometer output data into different SB and PA intensity categories, the following cut-offs will be used: sedentary behavior (accelerometer vector magnitude < 200 cpm), LPA light physical activity (200–2689 cpm) and moderate-to-vigorous physical activity (≥ 2690 cpm) [96].

*Maximal dynamic strength (estimated 1 RM)*. Participants of the CT group will perform incremental loading tests to estimate 1RM in all exercises with free weights, i.e., chest press, lateral arm raises, bent-over two-arm row, front squat, deadlift, and calf raises, preceded by a standardized general warm-up [56]. Participants will warm up by performing 2 x 10 reps of each exercise, using light loads to avoid injuries. We will use the protocol for 10RM testing following the National Strength and Conditioning Association guidelines [56]. After the completion of the warm-up sets, the instructors will adjust the loads so that the 10RM can be measured within 3 to 5 testing sets [56]. The process of testing will continue until a load allowing only 10 RM is determined [56]. This protocol will be conducted between 09:00 and 12:00 a.m. by two experienced instructors. The calculation of 1RM will be achieved based on the mathematical equation proposed by Brzicky [97]:

$$1RM=\frac{\left(100\;x\;rep\;wt\right)}{\left(102.78-2.78\;x\;number\;of\;repetitions\right)}$$

*Assessment of dietary intake*. Dietary habits will be assessed using a semi-quantitative Food Frequency Questionnaire (FFQ) [98], based on the previous 12 months. The FFQ was previously adapted for the Portuguese population [99, 100]. This instrument contains 82 food items, including 9 possible frequency responses, ranging from “never” to “six or more times per day” [100]. Any foods not reported in the FFQ but eaten regularly can be registered in an open-ended section [100]. To obtain nutrient intake, the frequency of consumption of each food item will be multiplied by the respective standard average portion (in grams), and by a seasonal variation factor for food consumed in specific seasons (0.25 are considered the average seasonality of three months) [100]. The conversion of food into nutrients will be performed using the software program Food Processor Plus (version 5.0, ESHA Research, Salem, OR), based on values from the US Department of Agriculture and from the composition of typical Portuguese foods that were included in this software [100, 101].

*Health*, *demographic*, *and lifestyle data*. Sociodemographic characteristics such as chronological age, gender, education degree, and marital status will be collected to characterize the sample and to adjust models. Health information will include past and current diseases (acute and/or chronic), medication, family history of metabolic diseases, dementia, or cognitive impairment. The “Pittsburg Sleep Quality Index” (PSQI) questionnaire will also be applied, before and after the trial, to assess subjective sleep quality over the previous month [102, 103]. Lifestyle information will include smoking history, consumption of alcoholic drinks, substance abuse and supplement use.

### Data analysis

Data analyses will be performed using SPSS Statistics version 25.0 (SPSS Inc., IBM Company, Chicago, Illinois, USA). Descriptive statistics (mean ± SD) will be performed for all variables in the analysis. The assumption of normality will be tested using histograms, normal probability plots and Shapiro-Wilk test. Chi-squared test will be performed to analyse sex proportions between groups. Assuming data normality, a two-way analysis of variance (ANOVA) for repeated measures will be applied for intra- and inter-group comparisons. In absence of normality, non-parametric Kruskall-Wallis test will be used. Bonferroni’s *post hoc* test will be performed if significant differences exist (alpha level set at 0.05). The magnitude of the global effect size will be calculated using Cohen’s effect size [104]. The Cohen’s d effect size is categorized according to the following criteria: *d* = < 0.20 (small), 0.21–0.79 (medium) and > 0.80 (large) [104]. The bivariate associations between the changes promoted by the exercise program and the different variables studied will be assessed by Spearman’s rank and Pearson’s coefficients. The strength of the associations will be classified as follows [105]: very high (0.90 < r < 1.00); high (0.70 < r < 0.90); moderate (0.50 < r < 0.70); low (0.30 < r < 0.50); little (0.10 < r < 0.30). Significance level set at *p* ≤ 0.05.

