### Estimated sample size

The sample size was calculated using a priori power analysis through the G*Power software version (3.1.9.2.), following the guidelines of Faul et al. [54]. For an effect size of 0.30, a sample size of 20 participants per group achieves 95% power to detect differences among the means versus the alternative of equal means using an F test with a 5% α-level. This analysis indicated a minimum total sample size required in this study. We plan to enrol 20% more persons to account for dropouts.

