#### Primary outcomes

*Biochemical assessment I*: *Fasting blood samples*. Blood collection will be performed in a seated position from the antecubital vein, at rest after a 12-hours overnight fast, and the blood samples will be aliquoted into kEDTA and serum tubes. The participants will be instructed to avoid extreme physical efforts 24 hours before the blood collection. Determination of blood counts will be done immediately after the blood collection, using an automated Coulter Ac•T diff Hematology Analyzer (Beckman Coulter^®^, Inc, USA). Biological samples will be centrifuged at 1500xg for 10-min and plasma and serum samples will be frozen at -80°Celsus (C) for posterior analysis. The levels of insulin, glucose, glycated haemoglobin (HbA1c), total cholesterol, low-density lipoprotein cholesterol (LDL-C), HDL-C, triglycerides, cytokines IL-1β, IL-1ra, IL-6, IL-10, transforming growth factor beta 1 (TGF-β), TNF-α, adiponectin and leptin will be analysed. Fasting glucose, triglycerides and cholesterol levels will be determined by standard enzymatic assays (ABX Pentra, Germany). Insulin, leptin and adiponectin will be analysed by ELISA (R&D Systems, UK). The Homeostatic model assessment (HOMA-IR) will be calculated using the Matthews formula [65]:

$$HOMA-IR=\frac{fasting\;glucose\;[mmol/L]\;x\;fasting\;insulin\;[\mu U/l]}{22.5}$$

Inflammatory cytokines will be analysed by ELISA kits (Thermofisher, UK) according to the manufacturer instructions. All blood collections for the biomarker analysis will be performed in the morning (between 07:30h – 10:30h) by a registered nurse.

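### No scale is pre-set for likely skewed primary biomarkers, and a normality check on the trial's own data picks the test; the raw scale, more than the check, costs power.

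*Protocol article*

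**What the plan says.** The Data analysis section of the protocol article states a rule with two branches.

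- The check: "The assumption of normality will be tested using histograms, normal probability plots and Shapiro-Wilk test". No cut-off is given. The text does not say whether observed values, changes or residuals are checked, or whether this is done by group and visit.
- If the check is passed: "Assuming data normality, a two-way analysis of variance (ANOVA) for repeated measures will be applied for intra- and inter-group comparisons".
- If it is not: "In absence of normality, non-parametric Kruskall-Wallis test will be used". The text does not say whether this is run on post values, on changes, or visit by visit.
- For description: "Descriptive statistics (mean ± SD) will be performed for all variables in the analysis".

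No transformation is named for any outcome. The primary outcomes include insulin, HOMA-IR, triglycerides and six cytokines; the list of blood markers ends with "adiponectin and leptin will be analysed". Salivary cortisol, α-amylase, immunoglobulin A and lysozyme are primary as well.

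**The concern.** Cytokines, hormones, triglycerides and salivary markers are positive concentrations, and HOMA-IR is a product of two of them. Right skew is the reasonable expectation, so a scale could be chosen before any data are seen. The plan instead waits for the data and then offers two analyses, neither on the log scale. Three things are at stake.

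1. **Power.** For a right-skewed marker with a proportional effect, both an ANOVA on raw values and a rank test on raw changes are less sensitive than a comparison of log changes.
2. **Consistency.** With about 20 per arm, whether a moderately skewed marker passes is partly chance, so related cytokines may be reported from different tests.
3. **The question answered.** The ANOVA addresses change within groups and group-by-time. Kruskal-Wallis compares independent groups on one value per person. Unless that value is the change, the branch taken alters the comparison as well as the method.

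A raw-scale mean ± SD for such markers is also driven by a few high values.

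**Working it through.** **The plan's own figure.** The Estimated sample size section says: "For an effect size of 0.30, a sample size of 20 participants per group achieves 95% power", "using an F test with a 5% α-level". Take 0.30 as Cohen's f, a group-by-time interaction with k = 2 groups and m = 2 visits, and an assumed correlation of 0.5:

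λ = f² × N × m / (1 − ρ) = 0.09 × 40 × 2 / 0.5 = 14.4, with 1 and 38 degrees of freedom. Power is 0.959, and N = 40 is the smallest total that reaches 95%.

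The figure reproduces for an ANOVA interaction. It does not describe the Kruskal-Wallis branch or an ANOVA on skewed values.

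**Inputs for the check.** From the protocol: 20 per arm (taken as the number analysed), 1:1 allocation and 5% significance. In Table 3, blood and saliva are taken at two visits, spirometry and quality of life at three. Assumed, because the protocol gives no SD, skewness or correlation: lognormal data, log-SD 0.3 to 0.7, pre-post correlation 0.60 or 0.75, a 25% reduction, and Shapiro-Wilk at 5% in each of the four group-by-visit cells as the deciding check.

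**Power for a two-visit biomarker** (simulation, 4000 trials per setting; correlation 0.60 / 0.75):

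| Log-SD | Rule, rank test on raw change | Log change | Loss (points) |
|---|---|---|---|
| 0.3 | 83% / 96% | 90% / 99% | 7 / 3 |
| 0.5 | 41% / 59% | 51% / 72% | 10 / 13 |
| 0.7 | 22% / 33% | 29% / 43% | 7 / 10 |

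The loss is 3 to 13 points. Independent re-runs agreed within simulation error.

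**Where the loss comes from.** At log-SD 0.5, the raw-scale group-by-time test with no check has 39% / 55% power, slightly below the 41% / 59% under the rule. The raw scale is therefore the main cause.

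**If Kruskal-Wallis is run on post values.** At log-SD 0.5 and correlation 0.75, the rule has about 44% power against 72% on the log scale: 72 − 44 = 28 points. This depends strongly on the correlation. With the effect set so that the log-scale test has 95% power, the loss is only about 1 to 4 points at correlation 0.5, but 14 to 25 at 0.7 and 23 to 38 at 0.8.

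**A larger effect.** With 95% design power on the log scale, correlation 0.5 and a rank test on change, the loss is 95.6 − 88.8 = 6.8 points at log-SD 0.3, 95.0 − 82.4 = 12.6 at 0.5, and 95.1 − 76.0 = 19.1 at 0.7.

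**How often truly normal outcomes would fail Shapiro-Wilk at 5%:**

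- four cells, treated as independent: 1 − 0.95⁴ = 18.5% (simulated 18.0% to 18.3%);
- six cells: 1 − 0.95⁶ = 26.5% (simulated 25.2% to 26.1%);
- arms pooled at each of two visits, or changes checked per group: about 9% to 10%;
- pooled group-centred changes: about 5%.

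**What that misrouting costs.** On normal data, always using the rank test on change gives 93.8% power against 95.0%, a loss of 1.2 points. Using it only after a failed check gave 67.4% against 67.6%. Type I error of the rule with a rank test on change stayed between 4% and 6%.

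**How far chance picks the test.** A marker with log-SD 0.3 passes in all four cells in about 36% of trials. At log-SD 0.5 about 6% to 7% pass, and at 0.7 about 1%, so the choice is open mainly for mildly skewed markers.

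**The case against.** The strongest reply is that the check does little harm. With a rank test on change as fallback it keeps the error rate, costs about a point or less on normal data, and does slightly better than an unconditional raw-scale ANOVA on skewed data. That is correct and limits the point.

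The section may also tempt a reader to infer that Shapiro-Wilk on the observed values alone decides, and that about one in five normal outcomes is sent to the wrong test. The text does not support this. Shapiro-Wilk stands beside two graphical checks, with no cut-off and no statement of what is checked. One in five fits only the four-cell reading, within a range of about 5% to 26%.

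It may further be said that the power comparison favours the log scale by construction, since the data were generated as lognormal with a proportional effect. This is fair: the figures show what is lost if that model is roughly right, not that it is right. The expectation of skew is likewise an assumption.

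Finally, transformations are often left to an analysis plan, which is not shown. That would excuse silence. Here the protocol says what happens to non-normal outcomes: they go to Kruskal-Wallis. A plan that followed this rule would inherit it.

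**Conclusion.** The point holds in a limited form. The stated rule fixes the analysis of the concentration biomarkers badly, because it sets no scale in advance and lets the data choose between two raw-scale analyses that need not test the same thing. That last defect needs no assumed figures.

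The cost in power is conditional. It is about 3 to 13 points under the assumptions in the table, and about 1 to 38 points across the wider settings tried, with the upper end arising when Kruskal-Wallis is run on post values and the correlation is high. The documents do not support a claim that the normality check is itself the main source of lost power, or that it inflates false positives when the fallback is a rank test on change. Its own harm is that the test behind a given marker is partly a matter of chance. The plan should be changed, but this does not threaten the validity of the trial.

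**What to change.** In the Data analysis section:

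- Remove the normality check as the means of choosing a test.
- Pre-set the natural-log scale for cytokines, insulin, HOMA-IR, leptin, adiponectin, triglycerides and salivary markers, and the original scale for lung function, blood pressure and questionnaire scores.
- Use one group-by-time model for all these outcomes, with graphical checks of its residuals. Keep a rank or bootstrap analysis as sensitivity only.
- Report logged outcomes as geometric means and between-group ratios with 95% CI in place of mean ± SD.

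This takes two or three sentences and no extra data. The small downside is that biomarker effects are given as ratios, not raw differences.
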